**Methods/design:**

This report describes a randomized, parallel-controlled trial with distributive concealment and evaluator blinding. A total of 84 eligible participants will be randomly assigned to the Tai Chi group or the control group in a 1:1 ratio. The participants in the Tai Chi group will receive 4 weeks of Tai Chi training: five 60-min sessions a week for a total of 20 sessions. The participants in the control group will not receive Tai Chi training. Both groups will receive medical treatment and routine rehabilitation training. The primary outcome measure is the mean change in the Fugl-Meyer Assessment Upper Extremity (FMA-UE) scale score between baseline and 4 weeks; the secondary outcomes are the mean changes in kinematic characteristics and the Wolf Motor Function Test (WMFT) and Stroke Impact Scale (SIS) scores. In addition, the corticomuscular coupling level and near-infrared brain functional imaging will be monitored to explore the mechanism by which Tai Chi improves upper limb function of stroke patients.

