Researchers have also found that enhanced coupling of the sensorimotor frontal-parietal cortex and muscle activation patterns is closely related to upper limb function recovery. Participants with high resting-state functional connectivity (rsFC) within and between motor networks—the contralateral primary motor cortex (M1) and the ipsilateral supplementary motor area SMA)—and frontal-parietal networks—between the dorsolateral prefrontal cortex (DLPFC) and the medial ventrolateral prefrontal cortex—have better hand function [12]. The functional connectivity (FC) of the ipsilateral premotor cortex (PMC) and the frontal-parietal region (bilateral precuneus and the DLPFC) are positively correlated with motor function. Compared with the healthy side, the FC of the ipsilateral somato-motor/sensory network (SMN) increases with bilateral frontal lobe (DLPFC) and the ipsilateral posterior parietal cortex (Pcu) during hand movement. The FC of the ipsilateral PMC and frontal-parietal region (bilateral Pcu and contralateral DLPFC) is positively correlated with motor function [13]. The motor frontal-parietal connection may be related to the neural processes related to motor execution and may be a potential biomarker for motor recovery after stroke [14].

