### Outcome measurements

The variables of this trial include basic characteristics, primary and secondary outcomes, and exploratory results. The basic characteristics will be determined from a questionnaire administered at baseline (1–2 weeks before randomization). The primary and secondary outcomes will be measured at baseline and at the end of the intervention (4 weeks after randomization). The exploratory results will be measured at baseline and at the end of the intervention (4 weeks after randomization). All results will be assessed by experienced assessors who do not know the group assignments of the participants.

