#### Primary outcome measures

The primary outcome measure is the change in the FMA-UE scale score from baseline to the end of the 4-week intervention. The FMA-UE scale includes 33 items divided into four subscales (arm, wrist, hand, and coordination), each scored on a 3-point sequential scale [37]. Scoring is based on performing independent actions inside and outside the synergy pattern. The maximum score of 66 corresponds to undamaged motor function. The FMA-UE scale is often used to classify the severity of stroke injury, and the scale shows good reliability and validity. A FMA-UE score between 32 and 57 indicates moderate upper limb injury and an FMA-UE score between 58 and 65 indicates mild injury of the contralateral arm. FMA-UE sensation (0–12), passive range of motion, and pain (0–24) will also be assessed.

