Effective connectivity (EC) analysis of the CLN is based on defining brain and muscle regions and ROIs. The basis for extracting ROIs from brain regions is that the brain map guides ROIs, and there are no overlapping regions to ensure the selection of functionally meaningful connected regions. The cortical reconstruction of the head model is used as the accurate geometric head model of the subjects. The EEG signals collected from the standard electrode leads of the international 10–20 system are represented on an accurate geometric model. First, the motor areas of the unaffected and affected sides are selected as ROIs, defined as Mu and Ma, respectively. The unaffected and affected somatosensory cortices are also considered to be ROIs, corresponding to Su and Sa, respectively. Finally, ROIs from unaffected and affected frontal and parietal regions are defined as Fu, FA, PAu, and PAa, respectively. For the muscle regions related to the two anatomical parts of the upper limb, according to the signals collected from the myoelectric electrodes on the affected side, the proximal (including the superior trapezius, the anterior deltoid, the posterior deltoid, the middle deltoid, the biceps brachii and the triceps brachii) and distal muscles (including the flexor carpi radialis and the extensor carpi radialis longus) of the upper limb are divided into two regions, which are defined as PM and DM. Based on the above 14 ROIs, the inflow index (IFI) and the outflow index (OFI) are used to determine the causal relationship between ROIs before and after training. To determine the difference in the average FcePDC value between the two groups in each frequency band before and after training, the FcePDC value calculated before training is defined as the baseline. The baseline changes are calculated by subtracting the baseline before training from the post-training values, and an independent-sample two-tailed *t*-test is performed to compare the changes between the two groups. In addition, repeated measures analysis of variance is used to test the statistical difference in the average FcePDC values in different information flow directions before and after training. Bonferroni correction is used to correct for multiple comparisons. The inter-group differences in network parameters (weighted clustering coefficient [C_W_] and weighted shortest path length [L_W_]) are tested with the Mann-Whitney *U* test. For EC analysis, the IFI and OFI values of ROI changes before and after training in the two groups are tested by paired two-tailed *t*-tests. The consistently paired *t*-test is used for the betweenness centrality parameter (BCX). The confidence level *α* is defined as 0.05.

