
Correlation analysis will also be employed. For the above brain functional features (based on brain imaging and graph theory analysis), brain regions with significant differences between groups are selected and relevant eigenvalues are extracted. The eigenvalues of functional brain connections of brain regions with significant differences or the partial and factor correlations between the eigenvalues of functional brain connections and upper limb scores are determined. Moreover, the factors that have the most significant impact on the cortex are analysed. The results are controlled for the influence of age, gender, education level, and other factors. Because the trial uses a single-blind design, the statisticians will conduct an interim analysis according to the label but without unblinding to guide the follow-up study.

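### The exploratory brain–limb correlation states neither change scores, baseline values nor treatment group, so on its plain reading a link with stroke severity could be taken for a Tai Chi mechanism

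*Protocol article*

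**What the plan says.** The neural measures are exploratory. According to the abstract they "will be monitored to explore the mechanism by which Tai Chi improves upper limb function of stroke patients". The last paragraph of the section on analysis of fNIRS, EEG and EMG data links them to limb function in three steps:

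- Selection: "brain regions with significant differences between groups are selected and relevant eigenvalues are extracted".
- Correlation: "the partial and factor correlations between the eigenvalues of functional brain connections and upper limb scores are determined".
- Control: "The results are controlled for the influence of age, gender, education level, and other factors".

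None of these sentences gives a time point or mentions change, baseline connectivity, baseline score or treatment group.

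Elsewhere the protocol says change when it means change. Under primary outcome measures: "The primary outcome measure is the change in the FMA-UE scale score from baseline to the end of the 4-week intervention". For the FcePDC group comparison: "The baseline changes are calculated by subtracting the baseline before training from the post-training values". Neither definition is carried into the correlation sentence.

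The background section reports from cited work that "The FC of the ipsilateral PMC and frontal-parietal region (bilateral Pcu and contralateral DLPFC) is positively correlated with motor function". It gives no coefficient. Both baselines will exist. FMA-UE is taken at baseline and week 4, and under outcome measurements "The exploratory results will be measured at baseline and at the end of the intervention (4 weeks after randomization".

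**The concern.** A mechanism claim needs patients whose connectivity changed more to be those whose arm function changed more. Correlating the two measures at one time point asks something else: whether patients with stronger connectivity also have better arms. The protocol's own background suggests that they do, regardless of training. Age, gender and education level do not capture stroke severity, so controlling for them leaves that link in place.

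The selection step adds a second route. Regions enter the correlation because the arms differ on them. If Tai Chi also raises FMA-UE, the arm difference alone makes the two measures correlate in the pooled sample, even when they are unrelated within each arm.

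At stake is the reading of the mechanism result. A significant correlation could be reported as support for a neural pathway when it reflects severity at entry, shared arm membership, or both.

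**Working it through.** The plan states no figure for this analysis, so there is none to reproduce. The question is how often the correlation is significant when no link between the changes exists.

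**Inputs from the document.** 84 randomised 1:1; 20% dropout, so 84 × 0.8 = 67.2, taken as n = 67; two-sided 0.05; planning effect size 0.683 (sample size section), borrowed as the arm effect in step 4.

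**Assumed, not in the document.** Baseline correlation r0 between connectivity and FMA-UE, 0.1 to 0.5; baseline-to-week-4 correlation (stability) s = 0.8 for each measure.

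**Model.** In SD units, week-4 value = s × baseline + noise with variance 1 − s² = 0.36. The noises for the two measures are independent, so there is no mechanism.

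**Step 1: week-4 values, no arm effect.** The expected correlation is s² × r0 = 0.64 × r0. The chance of significance is approximately P(Z > 1.96 − z) + P(Z < −1.96 − z), with z = atanh(0.64 r0) × √(67 − 3) = 8 × atanh(0.64 r0).

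| r0 | 0.64 r0 | z | Formula | Simulated (4000 trials) |
|---|---|---|---|---|
| 0.1 | 0.064 | 0.51 | 8% | 8% |
| 0.2 | 0.128 | 1.03 | 18% | 18% |
| 0.3 | 0.192 | 1.56 | 34% | 37% |
| 0.4 | 0.256 | 2.09 | 55% | 56% |
| 0.5 | 0.320 | 2.65 | 76% | 77% |

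For r0 of 0.3 to 0.5, changing s to 0.7 or 0.9 widens the range to 22% (0.3, 0.7) through 93% (0.5, 0.9) by the formula. Adding stand-ins for age, gender and education that are independent of severity does not help: at n = 68 the simulated range over the same settings is 22% to 92%.

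**Step 2: both baselines controlled, no arm effect.** Only the independent noises remain, so the expected correlation is 0. Simulated: about 5% throughout.

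**Step 3: change with change, no arm effect.** Each change has variance (1 − s)² + 0.36 = 0.04 + 0.36 = 0.40, and the covariance is 0.04 × r0. The correlation is 0.1 × r0, at most 0.05 here. Simulated: 5% to 7%. This check weakens if stability is low. At s = 0.5 and r0 = 0.4 the change correlation is (0.25 × 0.4)/(0.25 + 0.75) = 0.10, significant in about 13%.

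**Step 4: an arm effect of 0.683 SD on both measures, changes otherwise independent.** With 1:1 allocation, the arm contributes 0.683² × 0.25 = 0.1166 to each variance and to the covariance.

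- Both baselines controlled, group not: correlation 0.1166/(0.36 + 0.1166) = 0.245; z = atanh(0.245) × √(67 − 3 − 2) = 0.250 × 7.87 = 1.97, about 50%. Simulated: about 52%.
- Both baselines and group controlled: simulated about 5%.
- Change with change, group not controlled: (0.04 r0 + 0.1166)/(0.40 + 0.1166) = 0.233 to 0.264 for r0 = 0.1 to 0.5. Simulated: 49% to 60%.
- Change with change, group controlled: simulated 5% to 7%.

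Group and both baselines are therefore each needed. With group but no baselines, the week-4 correlation is still significant in 34% (r0 = 0.3) and 76% (r0 = 0.5).

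**The case against.** **Levels at week 4 are inferred.** The sentence gives no time point. It works on the features described above it, and the FcePDC group comparison there is on change, so a change reading is open. This stands, and it rules out saying that the plan definitely correlates levels. It does not remove the point. Even if the connectivity side were a change, the other side is still called scores, and the group test of the network parameters is given without any definition of change.

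**The list of controls is open.** Its unspecified remainder could include baseline values, and a full covariate list may sit in a document not shown. A reader might infer that baseline adjustment has been ruled out; the text does not support that. But the article does specify the variables, the selection, the method and three named controls. The most obvious confounder for its stated purpose is not among them.

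**The size is assumed.** No baseline correlation or stability is given. The cited finding comes from other studies, concerns functional connectivity rather than the EEG–EMG measure, and carries no coefficient. Entry criteria (muscle strength at least 3, Brunnstrom stage IV or above) and planning scores near 60 of 66 suggest a narrow severity range, which would weaken the link. At r0 of 0.1 to 0.2 the excess is modest: 8% to 18%.

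**The mechanism aim does not rest on this alone.** A reader might infer that this correlation is the plan's only bridge between brain and limb and that the mechanism aim fails with it. The document does not support that. The randomised comparison of FcePDC change bears on whether Tai Chi alters cortex–muscle coupling, and the behavioural section plans Pearson or Spearman correlations without naming variables.

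**Conclusion.** The point holds in limited form. As worded, the correlation does not secure the comparison a mechanism question needs. On its plain reading, a pre-existing severity link could pass as a mechanism; that it would do so is not shown. With independent changes, n = 67 and stability 0.8, a week-4 correlation is significant in about 8% of trials if the baseline correlation is 0.1 and about 76% if it is 0.5, against a nominal 5%. Both the baseline correlation and the stability are assumptions. If the investigators intend change scores, or already plan to adjust for baseline and group, the problem is one of wording only. The analysis is exploratory, and no primary or secondary result depends on it. It is still worth correcting because the mechanism is a stated aim and the remedy uses data already planned.

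**What to change.** In the correlation paragraph of the section on analysis of fNIRS, EEG and EMG data, state that:

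1. Week-4 connectivity will be correlated with week-4 FMA-UE by partial correlation, controlling for baseline connectivity, baseline FMA-UE and treatment group, besides the factors already listed.
2. Change-with-change correlation, adjusted for group, will be shown as a check.
3. Any plain correlation of values at one time point will be presented as descriptive of severity only.

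The cost is a few sentences. Both measures are already planned at baseline and week 4, and allocation is known, so no new data are needed. Group can enter under the coded labels, so the statisticians' blinding is kept. The downside is that adjusted correlations will usually be smaller than plain ones, so fewer will reach significance. Even the adjusted correlation shows association within arms and should be reported as consistent with a mechanism, not as proof of one.

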### Quality control

Before the implementation of the project, a standard research manual and CRF will be developed, and neuropsychological experts will be hired to carry out standardized training of the research evaluators so that they understand each step of the project implementation in detail. This endeavour will ensure the quality of the project. The clinical trial quality control committee will comprise one professor, two associate professors, and one doctor of the project team. The researchers will report the progress of the clinical trial to the clinical trial quality control committee every month for evaluation.

### Dissemination policy

The results will be published in peer-reviewed journals and communicated to the participants, health care professionals, and other relevant groups. All researchers and other colleagues who will participate in the future will become co-authors of this study based on their contributions.

## Discussion

The impairment of activities of daily living caused by upper limb dysfunction seriously affects the ability of post-stroke patients to return to their families, communities, and workplaces. However, there is no specific drug to treat upper limb dysfunction in clinical practice, and the reported rehabilitation training for upper limb dysfunction lacks high-quality evidence. A systematic review suggests that post-stroke patients can improve upper limb function through long-term upper limb rehabilitation training, but the medical cost of long-term upper limb rehabilitation training is high [41, 42]. Therefore, finding a safe, effective, well-defined, and low-cost rehabilitation treatment would substantially help patients return to society and reduce medical costs.

The recovery process of upper limb function is considered to require recovery of coupling the sensorimotor frontoparietal network and the upper limb muscle activation mode. Tai Chi represents an effective training method that can improve upper limb function of post-stroke patients. We propose that Tai Chi promotes the two-way sensorimotor control circuit of the cortex and muscle to promote regular muscle coordination and movement patterns to recover upper limb function. Can Tai Chi reduce the compensatory pattern to improve upper limb function after a stroke? Does Tai Chi promote the interaction between the sensorimotor frontal-parietal network and muscle activation patterns, thus promoting regular muscle coordination and movement patterns and reducing compensatory activities?

We will use several methods to improve the quality of this trial. Senior physical education teachers will act as Tai Chi coaches to ensure the quality of the Tai Chi training. The participants in the Tai Chi group will gather at a fixed time and place to practice. To control deviation caused by the amount of exercise, all participants will be required to keep an activity log. In addition, Tai Chi training will be supervised by two research assistants to ensure that both coaches and participants practice carefully. However, this trial may have some potential limitations. First, it is difficult for people involved in non-drug randomized controlled trials to be blind to the treatment. Indeed, in this study neither the coaches nor the participants can be blind to the treatment. Tai Chi coaches cannot participate in this study’s recruitment, evaluation results, or data analysis, and performance differences may be inevitable. Second, there is no follow-up. Finally, all participants will come from the same city, reducing the sample’s representativeness.

Tai Chi emphasizes the ‘unity of form and spirit’. When the ‘movement intention’ is generated, the corresponding brain regions are excited, and the resulting nerve impulses excite the muscle groups, thus completing the ‘voluntary movement’. This is the process of ‘the mind following the movement’ [43]. Through Tai Chi exercise, we can regulate the body, mind, and collaterals to promote recovery of upper limb function in post-stroke patients. This project will focus on the connection between the neural network (sensorimotor frontoparietal network) and the muscle network; consider the brain plasticity theory; and employ advanced research techniques such as fNIRS, EEG, and EMG to investigate the mechanism by which Tai Chi promotes functional recovery of upper limbs after stroke. This trial will advance the field, as the available research on the effect of Tai Chi on upper limb function after stroke has mainly focused on the overall effect on upper limb function and nerve excitability. These studies have not reported the mechanism for the interaction between the sensorimotor frontal-parietal cortex network and upper limb muscle activation mode of upper limb function.

A statement jointly released by the American Heart Association and the American Stroke Association predicts that by 2030, the United States’ expenditure on stroke and related disorders will increase to $240.67 billion [44]. Tai Chi has potential benefits for recovering upper limb motor function and daily living ability in post-stroke patients. At the same time, Tai Chi is a low-cost exercise, can save medical resources, reduces the economic burden on society and families, and has good economic benefits. In addition, this project provides evidence support for the rehabilitation effect of Tai Chi through high-quality randomized controlled trials and exploratory mechanisms research, which is conducive to the application and promotion of Tai Chi in hospitals, communities, and families.

In conclusion, this study is the first randomized controlled trial to systematically evaluate the effect of Tai Chi on the upper limb function of post-stroke patients from the perspective of neurophysiology. Significant results can provide rigorous evidence and a theoretical basis for applying Tai Chi training to post-stroke patients with upper limb dysfunction. The results will help understand the potential for adaptive brain reorganization and neuromuscular motor control mechanism, provide a reliable theoretical and experimental basis for the clinical application of Tai Chi, and provide a valuable reference for future research regarding how Tai Chi effectively improves upper limb function after stroke.

## Trial status

The first version of this trial was approved on March 4, 2022. The trial started on March 15, 2022. We hope to achieve our research objectives by December 2024.

## Protocol amendments

If there are any protocol amendments, the sponsor will be notified first, and then the principal investigator (PI) will notify the centre. The modified copy of the agreement will be sent to PI and added to the file on the researcher’s website. Any breach of protocol in this study will be fully recorded using the default report form, and the protocol will be updated in the clinical trial registry.

## Data Availability

In order to protect the privacy of participants, the data set generated or analysed during this study will not be made public. However, it can be obtained from the corresponding author upon reasonable request.

## Abbreviations

EEG: Electroencephalography
EMG: Electromyography
FcePDC: Extended partial directed coherence
FMA-UE: Fugl-Meyer Assessment of the Upper Extremity
fNIRS: Functional near-infrared spectroscopy
IFI: Inflow index
MAS: Modified Ashworth Scale
MMSE: Mini-Mental State Examination
OFI: Outflow index
WMFT: Wolf Motor Function Test
SIS: Stroke Impact Scale
